## Introduction

1.

Although spinal intradural extramedullary (IDEM) tumors grow slowly, the spinal canal is limited by its small volume, and the spinal cord and nerve roots are compressed or invaded by the tumor, which causes sensory, motor, and autonomic dysfunction (1). The treatment of spinal IDEM tumors focuses on removing tumor tissue and decompressing the nerve root and spinal cord to improve nerve function (2, 3). Traditional surgical methods include laminectomy (total laminectomy and hemilaminectomy), laminotomy, and laminoplasty (LP) (4). Among the available spinal surgeries with different indications, a “standard surgical procedure” for treating spinal IDEM tumors has not been determined. Owing to the development of minimally invasive spine surgery (MISS), the paraspinal mini-tubular technique (PMTT) has been introduced for treating IDEM tumors (5–7). Most studies reported that tubular spine surgeries reduced the volume of estimated blood loss (EBL) and shortened the length of hospital stay. The postoperative outcome of the patients was good, with fewer complications. These together promoted the development of MISS. A microscope-assisted PMTT has a larger operating space than endoscopy and a relatively wide range of indications, including various types of intervertebral disc herniation, spinal stenosis, spinal tumors, and spinal cord injuries (8). With the popularization and application of PMTT, the safety and effectiveness of treating spinal-related diseases have been increasingly recognized. Compared with traditional surgery, the microscope-assisted microtubular technique has the advantages of less tissue damage, fewer complications, shorter length of hospital stay, reduced postoperative pain, improved surgical efficiency, and reduced risk of spinal instability (9–11). To the best of our knowledge, prospective, randomized controlled trial studies with a large sample comparing the safety and effectiveness of the PMTT and LP in the treatment of spinal IDEM tumors, have not been conducted. Therefore, this study aims to explore the difference in the therapeutic effect of the PMTT and LP in the treatment of patients with spinal IDEM tumors through a prospective, multi-centered, non-inferiority randomized clinical trial. The main hypothesis is that PMTT has advantages in cost-effectiveness, and it is equivalent in safety and efficacy to LP.

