### Randomization and blinding

2.4.

Once written informed consent is obtained, patients would be randomized to undergo either the paravertebral approach or microtubular technique, or LP in a ratio of 1:1. The patients will be randomized using a block randomization model (block size: six). Computer-generated random number tables will be prepared by an experienced statistician. After baseline data are obtained, and a physical examination has been conducted, allocation of treatment will be performed by the computer system, and the results of the allocation will be provided to the surgeon in a concealed envelope one day before surgery. Due to the noticeable differences between the PMTT and LP procedures, blinding of the patients will not be strictly required. However, all researchers and data analysts will be blinded to the allocated intervention during the follow-up period of 2 years.

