### Outcome measurements

2.8.

Patients must have an indication for the surgery. The primary outcome variable is the JOA score. The secondary outcome variables include the VAS score, physical examination findings, length of hospital stay, expenses, and complications. Outcomes will be measured on the first postoperative day, and thereafter at the 1st week, and at 1, 3, 6, 12, and 24 months after surgical treatment. A physical examination will be conducted after 1 week, 1 month, and 12 months from the day of the surgery (Table 1). The non-inferiority margin for the primary outcome is five.

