### Secondary outcome

2.10.

Secondary outcomes include the gross tumor resection(GTR) rate, tumor recurrence rate, VAS, assessment of back and leg pain at rest, physical examination, length of hospital stay, expenses, and complications. One of the secondary outcomes was the VAS of pain. Perceived pain intensity was measured using the VAS score [pain scale ranging from 0 (no pain) to 100 mm (the worst pain imaginable)] (14). The pain will be assessed because most patients have pain in different regions. A physical examination will be conducted at 1, 6, and 12 months after the surgery. This will include the sphincter function test, muscle strength exercise, patellar and Achilles tendon reflex assessment, and sensory assessment of the affected spinal region. Muscle strength will be scored on a scale ranging from zero (no contraction) to five (normal muscle strength) (15).

The cost-effectiveness of the hospital stay will be evaluated by summarizing the cost of the surgical procedure and the number of days before discharge. The cost of the additional procedures in case of complications will be added to the total cost of the patient's hospital stay. The primary cost of treatment will include the cost of hospital admission, surgery, medication, rehabilitation, and other healthcare utilization. The details of these charges will be registered in a diary. Immediately after the operation, a systematic assessment of complications (including cerebrospinal fluid leakage, venous thromboembolism, wound infection, urinary tract infection, hematoma, and progressive neurological deficit) will be conducted by the surgeon and research nurse until patient discharge. Surgical data will include intraoperative spinal cord and nerve root injury, operative time, and intraoperative blood loss.

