#### Adverse and serious adverse events

2.10.1.

All adverse events related or not to the interventions will be reported during the complete study period. The list of adverse effects is adjacent segment instability, surgical site infection, worsening neurological symptoms, pain recurrence, dural tears, and CSF leakage.

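### Systematic complication assessment ends at discharge, an arm-dependent time, and the protocol does not say which of its three windows defines the compared complication outcome

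*Protocol article*

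**What the plan says.** All places are in the protocol article.

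- **Secondary outcome (2.10).** This is the only operational description of how complications are found. A systematic assessment starts right after the operation and "will be conducted by the surgeon and research nurse until patient discharge". Six events are named for it: "including cerebrospinal fluid leakage, venous thromboembolism, wound infection, urinary tract infection, hematoma, and progressive neurological deficit". The cost of extra procedures for complications is added to the cost of the hospital stay.
- **Introduction (1).** A shorter stay is expected with the tubular approach: "Most studies reported that tubular spine surgeries reduced the volume of estimated blood loss (EBL) and shortened the length of hospital stay". Compared with traditional surgery, the technique "has the advantages of less tissue damage, fewer complications, shorter length of hospital stay". No number of days is given.
- **Outcome measurements (2.8).** Stay and complications are both outcomes: "The secondary outcome variables include the VAS score, physical examination findings, length of hospital stay, expenses, and complications". Outcomes are then scheduled for day 1, week 1 and months 1, 3, 6, 12 and 24 after surgery, the same in both arms.
- **Adverse and serious adverse events (2.10.1).** "All adverse events related or not to the interventions will be reported during the complete study period". The list that follows covers surgical site infection, neurological worsening and CSF leakage. It does not name venous thromboembolism, urinary tract infection or hematoma.
- **Randomization and blinding (2.4).** The surgeon receives the allocation one day before surgery, yet "all researchers and data analysts will be blinded to the allocated intervention during the follow-up period of 2 years".

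**The concern.** A complication count that stops at discharge gives each patient an observation period equal to the postoperative stay. If one operation shortens the stay, its patients are actively observed for fewer days. Some events that would be recorded in hospital in the other arm then fall outside the window. With equal true risks, the arm that goes home earlier can look safer.

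The trial's hypothesis is that PMTT is equivalent to LP in safety and efficacy and has an advantage in cost-effectiveness. Complications bear directly on the safety part, and they enter the cost part through the procedures added to the hospital bill. The Introduction lists fewer complications and a shorter stay together as advantages of the technique. A window set by the stay could therefore help to produce the complication result that the trial expects.

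Sections 2.8 and 2.10.1 offer windows that do not depend on arm. What is at stake is which of the three windows the comparison will use, and whether events after discharge are sought as actively as events before it.

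**Working it through.** **1. The three windows side by side**

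| Section | Window | What is described |
|---|---|---|
| 2.10 | Surgery to discharge | Systematic assessment of six named complications by surgeon and research nurse |
| 2.8 | Day 1, week 1, months 1, 3, 6, 12, 24 | General schedule for all outcomes, complications among them |
| 2.10.1 | Whole study | Reporting of all adverse events; three of the six complications are not in its list |

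Only the first depends on arm, and only the first describes a procedure for finding complications. The schedule in 2.8 covers every outcome, including length of stay, which is settled at discharge. It therefore does not by itself establish a complication checklist at each visit. No sentence says which row supplies the compared outcome.

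**2. Size if only events before discharge count**

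The document gives no complication rate, stay or onset timing, so there is no stated figure to reproduce. All inputs here are assumptions: the same true 30-day risk R in both arms (10% or 20%), and postoperative stays of 5 vs 7, 7 vs 10, 5 vs 10 or 7 vs 14 days (PMTT vs LP).

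- Constant hazard: h = −ln(1 − R)/30, and the risk observed by day t is 1 − exp(−h·t).
- Front-loaded onset with mean τ days, truncated at day 30: the observed risk is R·F(t), with F(t) = (1 − exp(−t/τ))/(1 − exp(−30/τ)).

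Example with constant hazard, R = 10%, stays of 7 vs 10 days: h = 0.10536/30 = 0.003512. PMTT: 1 − exp(−0.02458) = 2.43%. LP: 1 − exp(−0.03512) = 3.45%. Ratio 0.70.

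Observed PMTT/LP ratio when the true ratio is 1.00:

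| Onset | 5 vs 7 | 7 vs 10 | 5 vs 10 | 7 vs 14 |
|---|---|---|---|---|
| Constant hazard, R = 10% | 0.72 | 0.70 | 0.50 | 0.51 |
| Constant hazard, R = 20% | 0.72 | 0.71 | 0.51 | 0.51 |
| Front-loaded, mean 7 days | 0.81 | 0.83 | 0.67 | 0.73 |
| Front-loaded, mean 3 days | 0.90 | 0.94 | 0.84 | 0.91 |
| Front-loaded, mean 1 day | 0.99 | 1.00 | 0.99 | 1.00 |

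In the front-loaded rows R cancels from the ratio.

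**3. Size if some events after discharge are also captured**

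Let c be the share of post-discharge events to day 30 that is recorded, equal in both arms. Observed risk is R·[F(t) + c·(1 − F(t))], so the spurious difference between arms is (1 − c)·R·[F(LP stay) − F(PMTT stay)]. For R = 10%, mean onset 7 days and stays of 7 vs 10 days, this is (1 − c) × (7.71% − 6.41%) = (1 − c) × 1.30 percentage points. It disappears only at c = 1, where the ratio is 1.00.

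**4. After a fixed window**

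With the same days counted from surgery and the same method of finding events in both arms, equal true risks give an expected ratio of 1.00. The sample size, which rests on the JOA score, does not change.

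**The case against.** The strongest answer is that capture after discharge is already provided and is neutral between arms. Section 2.8 names complications as an outcome and fixes visit dates from surgery. Section 2.10.1 covers all adverse events, which includes thromboembolism, urinary infection and hematoma whether or not its short list names them. On that reading, the discharge-bounded assessment is extra in-hospital surveillance, and no sentence excludes later events from the comparison. A condensed article may also leave the exact endpoint window to a fuller document.

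Much of this stands, and it rules out several stronger readings that a reader might infer:

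- **That PMTT will show fewer complications.** The documents do not support this. The bias arises only if the comparison uses the discharge-bounded count or if capture after discharge is less complete.
- **That the bias has a particular size.** Stays, rates and onset times are all assumed, and the range includes no bias.
- **That the operating surgeon alone judges complications.** The assessment is by the surgeon and the research nurse. Whether the blinding statement, which is tied to the follow-up period, covers the inpatient stay is arguable.
- **That complication costs are understated.** Section 2.10 also counts rehabilitation and other healthcare use, recorded in a diary, so costs after discharge may be included.

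The objection does not remove the inconsistency. The discharge limit is a stated choice and not a detail left out. It is attached to the only procedure described for finding complications, and the article does not say that the other two sections override it. Stating that events will be reported does not make reporting after discharge as complete as a systematic inpatient assessment.

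**Conclusion.** The point holds in a conditional form. The protocol ties its systematic complication assessment to discharge, expects discharge to come earlier with tubular surgery, and gives two other windows without saying which defines the compared outcome. If the discharge-bounded count is used, or if reporting after discharge is incomplete, the comparison can favour PMTT with equal true risks. The direction follows from the expected shorter stay, and would not apply if stays turned out equal.

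The size cannot be derived from the document. Under the assumed inputs the observed ratio runs from about 0.5 to 1.00. The low end needs a halved stay, onset spread evenly over 30 days and no capture after discharge. The high end applies when onset is within about a day or capture after discharge is full. Later-onset events are the most exposed.

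This concerns a secondary outcome and leaves the JOA comparison untouched. It should still be changed, because safety is part of the hypothesis and the remedy is cheap.

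**What to change.** - Reconcile sections 2.8, 2.10 and 2.10.1 by defining the compared complication outcome over one fixed window from surgery in both arms, for example any of the six named complications up to the existing 1-month visit.
- Apply the same six-item checklist at the existing 1-week and 1-month visits, whether or not the patient has been discharged.
- Count complication costs over the same window.
- State in section 2.4 or 2.10 that the surgeon's part of the in-hospital assessment is unblinded, since the surgeon receives the allocation before surgery.

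The cost is a little more work at visits that already exist, and somewhat higher observed complication rates in both arms because later events are found. No visit is added and the sample size does not change.

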#### Adverse and serious adverse events

2.10.1.

All adverse events related or not to the interventions will be reported during the complete study period. The list of adverse effects is adjacent segment instability, surgical site infection, worsening neurological symptoms, pain recurrence, dural tears, and CSF leakage.

### Sample size calculation

2.11.

The sample size for this study was calculated based on the JOA scores. Based on the preliminary data of our department, the mean difference and SD for the JOA used in the sample size calculation were as follows: mean 21.7, SD 5.8. The sample size for non-inferiority trials was calculated using the following: (1) significance level (alpha) of 0.05 and (2) power (beta) of 90%. We estimated that 112 patients would need to be included in each group. Accounting for 10% attrition and the actual situation of each participating center, 280 patients will be recruited in total. We intend to recruit patients within two years. Recruitment for the study began in October 2021.

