### Study description

2.1.

The FJMUUH05 trial is designed as a prospective, multi-center, non-inferiority RCT with two parallel groups in eight hospitals from seven provinces in China. A total of 280 patients aged 10–75 years with confirmed radiographic diagnosis and IDEM tumor lengths of less than three segments will be enrolled in this study. After the patients sign a written informed consent to participate, they will be randomized to one of the two groups: the PMTT group, which will receive paravertebral approach and microtubular technique treatment, and the LP group, which will receive laminoplasty treatment. The follow-up period will last for two years. The study is registered at https://www.chictr.org.cn, which can be accessed online (ChiCTR2100047582). Consent (version date January 21, 2021, V.1.0) will be obtained by an investigator who will comply with applicable regulatory requirements and adhere to the ethical principles of the Declaration of Helsinki. The time points, randomization, treatment allocation, and assessment are summarized in Figure 1.

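### Section 2.11's 112 per group at 90% power does not follow from its printed inputs, which at zero true difference give 24 to 30 per group

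*Protocol article*

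**What the plan says.** The study description (section 2.1) calls the trial a "prospective, multi-center, non-inferiority RCT with two parallel groups", and section 2.4 allocates "in a ratio of 1:1". In section 2.8, "The primary outcome variable is the JOA score" and "The non-inferiority margin for the primary outcome is five"; Table 2 repeats that margin.

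Section 2.11 says that "the mean difference and SD for the JOA used in the sample size calculation were as follows: mean 21.7, SD 5.8". It adds a "significance level (alpha) of 0.05" and 90% power, and concludes: "We estimated that 112 patients would need to be included in each group". The total follows: "Accounting for 10% attrition and the actual situation of each participating center, 280 patients will be recruited in total".

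Two inputs to a non-inferiority calculation are not given as usable values. The sidedness of alpha is not stated. The assumed true difference appears only in Table 2, where the expected JOA difference is listed as below 5. The introduction and the discussion both hypothesise that PMTT is equivalent to LP in safety and efficacy.

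**The concern.** A reader who puts the printed SD, margin, alpha and power into the usual formula, with no true difference, gets about a quarter of 112. The only number labelled a mean difference cannot fill the gap. A difference of 21.7 would be about three quarters of the 29-point scale (21.7/29 = 0.75), and Table 2 expects less than 5. It must be a mean score, and on the 29-point version, because section 2.9 gives the cervical JOA a maximum of 17.

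At stake is what the 90% power refers to. It could describe a margin of 5 with an assumed deficit, a tighter effective margin with no deficit, or a different SD. These imply different expectations of PMTT, and the text does not let a reader tell them apart.

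**Working it through.** **Inputs.** SD 5.8, alpha 0.05 and power 90% (section 2.11); margin M = 5 (section 2.8 and Table 2); 1:1 allocation (section 2.4). The true deficit of PMTT, d, is not fixed in the article, so it is varied. Alpha is read both as one-sided 0.05 and as one-sided 0.025 (two-sided 0.05).

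**Formula.** n per group = 2 × SD² × (z_alpha + z_power)² / (M − d)², with 2 × 5.8² = 67.28.

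**Attempt to reproduce 112 with d = 0.**
- One-sided 0.025: 67.28 × (1.960 + 1.2816)² / 25 = 28.28, so 29 (30 by exact t).
- One-sided 0.05: 67.28 × (1.645 + 1.2816)² / 25 = 23.05, so 24 (24 by exact t).

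Other methods at d = 0 do not reach 112:
- Two one-sided equivalence tests: 30 (0.05 per side) or 35 (0.025 per side).
- Worst-case efficiency loss for a rank test: about 34.
- SD multiplied by √2: 47 (one-sided 0.05) or 57 (one-sided 0.025).

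**Power at 112 per group, d = 0, M = 5.** The standard error is 5.8 × √(2/112) = 0.775. Then 5/0.775 − 1.960 = 4.49, so power exceeds 99.99%. It is higher still at one-sided 0.05.

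**Solving backwards for 112.** The distance M − d that 112 per group supports at 90% power is 5.8 × (z_alpha + z_power) × √(2/112). This is 2.51 at one-sided 0.025 and 2.27 at one-sided 0.05. So 112 is recovered by any one of:
- M = 5 and a PMTT deficit of 5 − 2.51 = 2.49 (one-sided 0.025) or 5 − 2.27 = 2.73 (one-sided 0.05);
- d = 0 and an effective margin of 2.51 or 2.27;
- d = 0, M = 5 and an SD of 11.5 or 12.8.

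The required n depends strongly on d (M = 5, SD 5.8, normal formula):

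| Assumed PMTT deficit | n per group, one-sided 0.025 | n per group, one-sided 0.05 |
|---|---|---|
| 0 | 29 | 24 |
| 1 | 45 | 37 |
| 2 | 79 | 65 |
| 2.5 | 114 | 93 |
| 3 | 177 | 145 |

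**Attrition.** 112/0.9 = 124.4, so 125 per group and 250 in total. The planned total is 280, which is 30 more. With 10% loss, 280 leaves 252 evaluable patients, or 126 per group.

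**The case against.** The strongest reply is that SD, margin, alpha and power do not fix a non-inferiority sample size: the assumed true difference is also needed. The article never says it is zero, and Table 2 leaves it anywhere below 5. A deficit of about 2.49 (one-sided 0.025) or 2.73 (one-sided 0.05) lies inside that range and returns 112 with the margin and SD as printed. The full protocol may state such a value.

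This part stands. A reader might infer that the size, margin and power describe different trials, or that 112 is about four times too large without qualification. The article does not support either, because both conclusions need zero difference as a premise.

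The reply does not clear section 2.11. A range below 5 is not a design value: n grows without limit as d approaches 5. Table 2 gives the same pair of entries for all four outcomes, including muscle strength, which section 2.10 scores from 0 to 5, so it is hard to read as a considered JOA assumption. A planned deficit of about 2.5 points would also sit awkwardly with the equivalence hypothesis. And the article does print a calculation with inputs and a result; those inputs do not produce that result.

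On attrition, a reader might infer that 280 really allows for 20% loss, since 112/0.8 = 140 per group. The article attributes the total to 10% attrition plus circumstances at the centres. The second part is unquantified, but it is a stated reason.

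**Conclusion.** The point holds in a conditional form: 112 per group at 90% power does not follow from the inputs printed in section 2.11. With zero true difference, SD 5.8 and margin 5, the requirement is 24 to 30 per group, and power at 112 exceeds 99.99%. Those figures rest on the zero-difference reading, which fits the stated hypothesis but is not itself stated. Recovering 112 needs an input the article does not give, and the back-solved values are inferences, not evidence of what the sponsor assumed. The label on 21.7 is wrong on any reading.

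On the zero-difference reading the trial is larger than needed; it is neither underpowered nor exposed to an inflated type I error. The defect is that a sample size and power on which the trial relies are wrong or incomplete as written.

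A reader might also infer that the margin ought to be 2.5. The documents do not support that: the article gives 5 twice and 2.5 nowhere. If 112 was built on a deficit near 2.5, a margin of 2.5 would leave power of only about 2.5%.

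**What to change.** Restate section 2.11 so that it reproduces:

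- Give the assumed true difference, the sidedness of alpha, the margin and the SD that produced 112.
- Relabel 21.7 as a mean score.
- If the assumed difference is zero with margin 5, say that about 24 to 30 per group are required and that the planned 280 gives power above 99%.
- If a deficit of about 2.5 points was assumed, state it and reconcile it with the equivalence hypothesis.
- Split the step from 224 to 280 into 10% attrition (to 250) and the centre-related allowance (the other 30).

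This is a change of wording and needs no extra patients. A tighter margin is an option, not a required correction. For example, 2.5 with zero difference needs 114 per group at one-sided 0.025, and 126 evaluable per group would give about 93% power. It would need its own clinical justification. Because recruitment began in October 2021 and 11 patients were already included, it would be a substantive design change.
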